## Abstract

**Background:**

Hypoxia is a very common adverse event that occurs during gastrointestinal endoscopy under sedation, especially in older patients, owing to limited reservation of heart, brain, lung, and other organs. Prolonged or severe hypoxia can cause ischemia of the coronary artery and permanent nervous system damage, and even result in death. Hence, it is imperative to reduce or prevent hypoxia during gastrointestinal endoscopy under sedation in older patients. Although several oxygen delivery methods would reduce hypoxia during this procedure, early detection of respiratory depression and early administration of intervention would be the best method to reduce or even confirm the hypoxia. Capnographic monitoring is reportedly more sensitive for detecting respiratory depression before the onset of hypoxia than the current clinical routine monitoring of pulse oxygen saturation; however, its effect is controversial. Therefore, in this study, we aimed to improve the safety of gastrointestinal endoscopy under sedation in older patients.

**Methods:**

A multicenter, randomized, single-blind, two-arm parallel-group, controlled with an active comparator, interventional superiority clinical trial will be conducted to evaluate the impact of an additional capnographic monitoring-based intervention on the incidence of hypoxia in older patients. Patients (*n* = 1800) scheduled for gastrointestinal endoscopy with propofol sedation will be randomly assigned to either a control or interventional arm, wherein standard or capnographic monitoring is implemented, respectively.

**Discussion:**

This study primarily aims to examine whether an additional capnographic monitoring-based intervention can reduce the incidence of hypoxia in older patients during gastrointestinal endoscopy under propofol and sufentanil sedation. The results of this study may extensively impact gastrointestinal endoscopy under sedation and the development of associated guidelines.

**Trial registration:**

ClinicalTrials.gov NCT05030870. Registered on September 1, 2021.

**Supplementary Information:**

The online version contains supplementary material available at 10.1186/s13063-023-07208-0.

## Administrative information

Note: the numbers in curly brackets in this protocol refer to SPIRIT checklist item numbers. The order of the items has been modified to group similar items (see http://www.equator-network.org/reporting-guidelines/spirit-2013-statement-defining-standard-protocol-items-for-clinical-trials/).

## Introduction

### Background and rationale{6a}

The sedation rate of gastrointestinal endoscopy varies in different countries. In China, the overall sedation rate for gastrointestinal endoscopy is ~50% [1], whereas in the USA, >98% gastrointestinal endoscopy procedures are performed under sedation [2, 3]. Cardiopulmonary complications, especially hypoxia, are the most common complications that occur during gastrointestinal endoscopy under sedation. Prolonged or severe hypoxia can cause ischemia of the coronary artery and permanent nervous system damage or even result in death [4, 5]. Thus, determining a method to reduce hypoxia incidence in gastrointestinal endoscopy under sedation is crucial.

Compared with the current clinical routine monitoring of pulse oxygen saturation (SpO_2_), capnographic monitoring can detect hypoventilation and respiratory depression earlier, thereby helping in providing earlier intervention [6]. Therefore, it is believed that capnographic monitoring would reduce the incidence of hypoxia. Nevertheless, whether capnographic monitoring should be routinely performed during gastrointestinal endoscopy under sedation with propofol remains controversial.

There are two major studies regarding this subject; however, their results are discrepant. The first investigation, a randomized, controlled study (ColoCap Study) conducted by Beltz et al., confirmed that additional capnographic monitoring of ventilatory activity in ASA I–III patients reduces the incidence of hypoxia during propofol sedation for colonscopy [7]. However, the second investigation, a cohort study, reported that additional capnographic monitoring did not improve patient safety or satisfaction, but it did increase the cost [8]. The fundamental problem was that the initial oxygen flow in the ColoCap Study was only 2 L/min, which is inconsistent with that in clinical practice (3–4 L/min). This inconsistency resulted in a hypoxia incidence of >50% in the control group. Another limitation of the ColoCap Study was that the depth of sedation between the two groups may have been inconsistent. Although the cohort study was designed to closely mimic clinical practice, it did not yield positive results. These conflicting results indicate that there is insufficient evidence regarding routine capnographic monitoring in patients.

Older patients comprise a vulnerable group who are more susceptible to hypoxia during gastrointestinal endoscopy performed under drug-induced sedation [9, 10]. However, to the best of our knowledge, whether this vulnerable group requires routine monitoring for capnography has not been investigated. Therefore, this study was designed to improve the security of gastrointestinal endoscopy under sedation in older patients.

### Objectives {7}

Our aim is to investigate whether an additional capnographic monitoring-based intervention can reduce hypoxia incidence in older patients undergoing gastrointestinal endoscopy under sedation. Our primary objective is to measure the incidence of hypoxia (75% ≤ SpO_2_ < 90% for < 60 s). Our secondary objective is to measure the incidences of subclinical respiratory depression (90% ≤ SpO_2_ < 95%), severe hypoxia (SpO_2_ < 75% or 75% ≤ SpO_2_ < 90% for ≥60 s), and other adverse events (AEs) recorded via tools proposed by the World Society of Intravenous Anesthesia International Sedation Task Force. We predict that additional capnographic monitoring of ventilatory activity will reduce hypoxia incidence during propofol sedation for gastrointestinal endoscopy in older patients. Our aim is to provide credible evidence regarding reduced hypoxia incidence in older patients.

### Trial design {8}

This study is a multicenter, randomized, single-blind, two-arm parallel-group, controlled with an active comparator, interventional superiority clinical trial. We intend to evaluate the impact of an additional capnographic monitoring-based intervention on hypoxia incidence in older patients.

This trial was conducted under the recommendations of the Standard Protocol Items: Recommendations for Interventional Trials (SPIRIT). The trial was registered on ClinicalTrials.gov (No. NCT05030870) on September 1, 2021. We presented the trial registration data in the form of Supplemental data.

## Methods: participants, interventions, and outcomes

### Study setting {9}

This study will enroll ~1800 participants from the Renji Hospital Shanghai Jiao Tong University School of Medicine, Henan Provincial People's Hospital, and Qilu Hospital of Shandong University. The ethics committee of the Renji Hospital Shanghai Jiao Tong University School of Medicine approved and supported this clinical trial (KY-2021014).

### Eligibility criteria {10}

This clinical trial has three centers that recruited patients. A summary of the inclusion and exclusion criteria is presented in Table 1.

**Table 1 Tab1:** Inclusion/exclusion criteria

Inclusion criteria	Exclusion criteria
1) Aged ≥65 and <80 years	1) Coagulation disorders or a tendency of nose bleeding
2) Scheduled to undergo gastrointestinal endoscopy procedure with sedation	2) An episode/exacerbation of congestive heart failure that requires a change in medication, diet, or hospitalization from any cause in the past 6 months
3) Signed the informed consent form	3) Severe aortic stenosis or mitral stenosis
4) American Society of Anesthesiologists (ASA) classification I-II	4) Cardiac surgery involving thoracotomy (e.g., coronary artery bypass graft, valve replacement surgery) in the past 6 months
	5) Acute myocardial infarction in the past 6 months
	6) Acute arrhythmia (including any tachycardia or bradycardia) with fluid of hemodynamics instability
	7) Diagnosed with chronic obstructive pulmonary disease or current other acute or chronic lung disease requiring supplemental chronic or intermittent oxygen therapy
	8) Preexisting bradycardia (heart rate <50/min), or hypoxia (SaO_2_ < 90%)
	9) Need supplemental oxygen because of preexisting diseases
	10) Emergency procedure or surgery
	11) Multiple trauma
	12) Upper respiratory tract infection
	13) Allergy to propofol or tape and adhesives

### Who will take informed consent? {26a}

Trained anesthesiologists will explain this trial to the potential participants in detail, and the informed consent form will be provided. Participants can decide whether they wish to participate in the trial after sufficient time to deliberate. Subsequently, the participant or his/her trustee or guardian can sign the informed consent form, and they can withdraw at any time during the trial. Following this, baseline data will be collected from the patients, and they will be randomly allocated using the central random system. Participants can contact our team if they have any health concerns during the trial. The entire process of recruiting participants and obtaining their consent by the members of the research team will be performed in accordance with good clinical practice (GCP). In case of any AEs during the trial related to the study procedure or not, the researchers will immediately report to the director in charge of the clinical trial of the research institution and contact [name].

### Additional consent provisions for collection and use of participant data and biological specimens {26b}

Not applicable as no participant data and biological specimens were collected or used in ancillary studies.

## Interventions

### Explanation for the choice of comparators {6b}

For the choice of comparators, the central randomization system will be used for each study site. Following randomization, the participants will receive either standard monitoring (Arm2) or additional capnography (Arm1). The comparator in this trial is standard monitoring alone (Arm2).

### Intervention description {11a}

Capnography-blinded arm (Arm2) and capnography-open arm (Arm1) constitute the interventions for the participants in this trial. The capnography-blinded arm involves standard monitoring, and the capnography-open arm involves additional capnography.

In both the groups, standard monitoring will include determining the heart rate, SpO_2_, electrocardiogram, and noninvasive blood pressure of the selected patients. In the capnography-open arm, a sampling line will be connected to a bedside portable monitor (Capnostream 20; Medtronic, Inc.) to ensure that the capnographic data of the patients are available for the additional noninvasive assessment of ventilation. A nasal cannula equipped with an oral sampling port to accommodate mouth breathers provided 2 L/min oxygen and continuously sampled CO_2_ content of both inspired and expired patient gas. The sampling line was connected to a portable bedside monitor (Capnostream 20; Medtronic, Inc.) displaying the time-based CO_2_ graphic waveform, numerical CO_2_ partial pressure (mmHg), derived respiratory rate, and SpO_2_ via integrated pulse oximetry. The height, shape, and rhythm of the capnogram provide a real-time assessment of ventilatory function. In the presence of supplemental oxygen during inspiration, the samples essentially contain no CO_2_, and the samples represent alveolar CO_2_ concentration during expiration, with a small amount of gas containing no CO_2_ from the patient physiologic dead space. For alveolar hyperventilation, the samples comprise reduced to no CO_2_. In the capnography-blinded arm, no sampling line will be connected to the bedside portable monitor, and the capnographic data of the patients will not be visible to ensure that only the integrated pulse oximetric readout of the monitor is visible.

Table 2 lists the AEs of anesthesia and sedation.

**Table 2 Tab2:** Adverse events of anesthesia and sedation

**Step 1:Was there one or more adverse events associated with this sedation encounter?**				
□ No, this form is now complete.	□ Yes, fill out the remainder of the form below.			
**Step 2: Please DESCRIBE the adverse event(s). Check all that apply.**				
**Minimal risk descriptors**	**Minor risk descriptors**		**Sentinel risk descriptors**	
□ Vomiting/retching	□ Oxygen desaturation (75–90%) for < 60s		□ Oxygen desaturation, severe (<75% at any time) or prolonged (<90% for >60s)	Other, specify below
□ Sub-clinical respiratory depression^a^	□ Apnoea not prolonged		□ Apnoea, prolonged (>60s)	
□ Muscle rigidity, Myoclonus	□ Airway obstruction		□ Cardiovascular collapse/shock^g^	
□ Hypersalivation	□ Failed sedation^e^		□ Cardiac arrest/absent pulse	
□ Paradoxical response^b^	□ Allergic reaction without anaphylaxis			
□ Recovery agitation^c^	□ Bradycardiat^f^			
□ Prolonged recovery^d^	□ Tachycardia^f^			
	□ Hypotension^f^			
	□ Hypertension^f^			
	□ Seizure			
**Step 3: Please note the INTERVENTIONS performed to treat the adverse events(s). Check all that apply.**				
**Minimal risk**	**Minor risk**	**Moderate risk**	**Sentinel intervention**	
□ No intervention performed	□ Airway repositioning	□ Bag valve mask-assisted ventilation	□ Chest compressions	Other, specify below
□ Tactile stimulation	□ Tactile stimulation	□ Laryngeal mask airway	□ Tracheal intubation	
□ Additional sedative(s)	Or the administration of:	□ Ora/nasal airway	Or the administration of:	
□ Antiemetic	□ Supplemental oxygen, new or increased	□ CPAP	□ Neuromuscular block	
□ Antihistamine	□ Antisialogogue	Or the administration of:	□ Pressor/epinephrine	
		□ Reversal agents	□ Atropine to treat bradycardia	
		□ Rapid i.v.fluids		
		□ Anticonvulsant i.v.		
**Step 4: Please note the OUTCOME of the adverse events(s). Check all that apply.**				
**Minimal risk outcome**	**Moderate risk outcome**		**Sentinel outcome**	
□ No adverse outcome	□ Unplanned hospitalization or escalation of care^h^		□ Death	Other, specify below
			□ Permanent neurological deficit	
			□ Pulmonary aspiration syndrome^i^	
**Step 5: Assign a SEVERITY rating to the adverse event(s) associated with this sedation encounter.**				
If there are any options checked in the Sentinel columns above, then this is a Sentinel adverse event^j^.				
If the most serious option(s) checked above are Moderate risk, then this is a Moderate risk adverse event^k^.				
If the most serious option(s) checked above are Minor risk, then this is a Minor risk adverse event^l^.				
If the most serious option(s) checked above are Minimal risk, then this is a Minimal risk adverse event^m^.				

Footnotes:

^a^ “Sub-clinical respiratory depression” is defined as capnographic abnormalities suggesting respiratory depression that do not manifest clinically

^b^ “Paradoxical response” is defined as unanticipated restlessness or agitation in response to sedatives

^c^ “Recovery agitation” is defined as abnormal patient affect or behaviors during the recovery phase that can include crying, agitation, delirium, dysphoria, hallucinations, or nightmares

^d^ “Prolonged recovery” is defined as failure to return to baseline clinical status within 2 hours

^e^ “Failed sedation” is defined as inability to attain suitable conditions to humanely perform the procedure

^f^ Alteration in vitals signs (bradycardia, tachycardia, hypotension, hypertension) is defined as a change of >25% from baseline

^g^ “Cardiovascular collapse/shock” is defined as clinical evidence of inadequate perfusion

^h^ Examples of “escalation of care” include transfer from ward to intensive care, and prolonged hospitalization

^i^ “Pulmonary aspiration syndrome” is defined as known or suspected inhalation of foreign material such as gastric contents into the respiratory tract associated with new or worsening respiratory signs

^j^ “Sentinel” adverse events are those critical enough to represent real or serious imminent risk of serious and major patient injury. Once recognized, they warrant immediate and aggressive rescue interventions. Once clinically concluded, they warrant immediate reporting within sedation care systems and the highest level of peer scrutiny for continuous quality improvement

^k^ “Moderate” adverse events are those that, while not sentinel, are serious enough to quickly endanger the patient if not promptly managed. Once clinically concluded, they warrant timely reporting within sedation care systems and periodic peer scrutiny for continuous quality improvement

^l^ “Minor” adverse events are those encountered periodically in most sedation settings, and that pose little threat given appropriate sedationist skills and monitoring

^m^ “Minimal” adverse events are those that alone present no danger of permanent harm to the patient

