#### Secondary outcome measures

The secondary outcomes comprise the following:The incidence of subclinical respiratory depression (90% ≤ SpO_2_ < 95%) in the two groups from the beginning to the end of the operation.The incidence of severe hypoxia (SpO_2_ < 75% or 75% ≤ SpO_2_ < 90% for ≥60 s) in the two groups from the beginning to the end of the operation.The incidence of other AEs recorded via tools proposed by the World Society of Intravenous Anesthesia International Sedation Task Force.

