**Others**						
Gastroscope procedure time				**×**		
Combined medication	**×**	**×**	**×**	**×**	**×**	**×**

When the participants will enter the gastrointestinal endoscopic operating room, they will be screened for eligibility by the investigator. If they meet the inclusion criteria but not the exclusion criteria, the investigator will provide them with the fully informed consent form. After signing the informed consent form, the patients will be allocated to either the capnographic monitoring group or the control group via the central randomization system.

In the capnographic monitoring group, the criteria for apnea is the absence of exhaled CO_2_; altered ventilation is defined as end-tidal CO_2_ reduced by more than half of the baseline, as shown by the capnogram; and the definition of hypoxia is 75%<SpO_2_ < 90%, <60s. In the control group, hypoxia is defined as SpO_2_ <90%.

In both the groups, any sign of apnea, altered ventilation, or hypoxia that prompts an intervention will comprise (i) increasing oxygen supplementation, (ii) a chin lift or jaw thrust maneuver, (iii) insertion of the oropharyngeal or nasopharyngeal airway with a chin lift or jaw thrust maneuver, (iv) artificial mask ventilation, and (v) tracheal intubation.

The duration of surgery is defined as the time from the beginning to the end of the gastrointestinal endoscopy, excluding the time of resuscitation.

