### Concealment mechanism {16b}

After obtaining the signed informed consent, the participants will be randomly assigned to the standard or additional capnographic monitoring group according to the central randomization system. The random results, random number, and their relationship with groups will be kept confidential from the participants throughout the trial. The same nasal cannula with a CO_2_-collecting device will be used in both groups and connected to the capnographic monitoring device. The participants will not be aware of their own and others’ grouping before, during, and following gastrointestinal endoscopy.

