#### Additional analyses

Safety analysis: general safety evaluations will be based on the incidence and type of AEs. Safety variables will be tabulated and presented for all the patients in safety sets. AEs will be coded using the tools proposed by the World Society of Intravenous Anesthesia International Sedation Task Force. The number (%) of subjects with any AEs will be summarized and compared via *χ*^2^ test, continuity correction *χ*^2^ test, or Fisher’s exact test.

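### The adverse event form defines sub-clinical respiratory depression by capnography, which staff can see in one arm only, so the between-arm comparison of any adverse event is inflated in the capnography arm by detection alone

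*Protocol article*

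**What the plan says.** **Two definitions of one term.** Footnote a to Table 2 says that sub-clinical respiratory depression "is defined as capnographic abnormalities suggesting respiratory depression that do not manifest clinically". The secondary outcomes list "The incidence of subclinical respiratory depression (90% ≤ SpO_2_ < 95%) in the two groups from the beginning to the end of the operation", and Objectives {7} gives the same SpO2 band. Table 3 and the statistical analysis plan paragraph call the outcome sub-clinical hypoxia.

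**Visibility and blinding.** Intervention description {11a} states: "In the capnography-blinded arm, no sampling line will be connected to the bedside portable monitor". It adds that control-arm capnographic data will not be visible. Who will be blinded {17a} limits blinding to participants. Concealment mechanism {16b}, however, says that the same CO2-collecting cannula "will be used in both groups and connected to the capnographic monitoring device", and {17a} also describes the line as connected to the monitor.

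**Apnoea.** The text after Table 3 reads: "In the capnographic monitoring group, the criteria for apnea is the absence of exhaled CO_2". It gives no apnoea criterion for the control group; the corresponding control sentence concerns only SpO2 below 90%. On the form, apnoea is a minor item, or a sentinel item if longer than 60 s. No footnote defines it.

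**Analysis.** Additional analyses, under Statistical methods {20a}, codes adverse events with this tool and continues: "The number (%) of subjects with any AEs will be summarized and compared via" a chi-square, continuity-corrected or Fisher test.

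**The concern.** A capnographic abnormality without clinical signs cannot be noticed by someone who has no capnogram. If staff complete the form as written, a near-zero control count for this item is built in and says nothing about the effect of monitoring. Because the item counts as an adverse event, the excess passes into the test of any adverse event and into any tabulation of the Step 5 severity grade.

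Apnoea adds to this. A CO2 criterion in one arm and none in the other means unequal sensitivity, and prolonged apnoea carries the highest grade on the form.

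At stake is the safety comparison. A formal test could show more adverse events with capnography when the true rates are the same. Separately, two assessors could each follow the protocol and code the same patient differently, because the term has two meanings.

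**Working it through.** **1. Can each arm generate the event?**

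| Item | Capnography arm | Control arm |
|---|---|---|
| Sub-clinical respiratory depression, SpO2 90% to <95% (objectives, secondary outcomes) | Yes | Yes |
| Sub-clinical respiratory depression, Table 2 footnote a | Yes | Essentially no: capnogram not visible, and no clinical sign by definition |
| Apnoea | CO2 criterion stated | No criterion stated; clinically observed apnoea can be recorded |
| Primary outcome (SpO2) | Yes | Yes |

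The article states no hidden recording or later masked reading of control-arm traces that would equalise the second and third rows.

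**2. The plan's own sample size**, needed only for the scale of the illustration. Inputs from Sample size {14}: 8% versus 4%, two-sided 5%, power 90%, 1:1 allocation, 10% dropout.
- Pooled-variance formula: n = [1.960·√(2·0.06·0.94) + 1.2816·√(0.08·0.92 + 0.04·0.96)]² / 0.04² = 739 per arm.
- With continuity correction, n/4·[1 + √(1 + 4/(n·0.04))]² = 788 per arm.
- Dropout: 788/0.90 = 876 per arm, 1752 in total, within 3% of the stated figure of about 1800. The sample size is not in dispute.
- For the illustration: 1800/2 = 900 per arm, or 900 × 0.90 = 810 after dropout.

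**3. Size of the detection effect.** The protocol gives neither a rate of capnography-only events nor a rate of any adverse event, so both are assumptions. Let the true rates be equal. Let the control arm record a base rate b, and the capnography arm b + x, where x is the share of patients whose only event is a capnographic abnormality. The chance of a significant two-sided result is Φ[(x − 1.960·SE0)/SE1], with SE0 the pooled and SE1 the unpooled standard error.

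Example: b = 8%, x = 4 points, 810 per arm. SE0 = √(2·0.10·0.90/810) = 0.01491. SE1 = √((0.12·0.88 + 0.08·0.92)/810) = 0.01487. Then (0.04 − 1.960·0.01491)/0.01487 = 0.725, and Φ = 0.77.

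| Base b | Extra x | 810 per arm | 900 per arm |
|---|---|---|---|
| 8% | 4 points | 77% | 81% |
| 8% | 5 points | 91% | 93% |
| 8% | 6 points | 97% | 98% |
| 20% | 4 points | 49% | 54% |
| 20% | 8 points | 97% | 98% |
| 30% | 4 points | 41% | 44% |

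The nominal figure in every cell is 5%. The 8% is the protocol's hypoxia rate. Any adverse event covers every item on the form, including changes in vital signs of more than 25%, so its base is probably higher and the lower rows are more relevant.

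**4. Partial detection.** Suppose other events occur independently in 20% of patients and the true capnographic event rate is 10%. The capnography arm then shows 1 − 0.80·0.90 = 28%. If the control arm detects none, it shows 20%, and false significance is about 96% at 810 per arm. If it detects half, it shows 1 − 0.80·0.95 = 24%, and the figure is 45%.

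**The case against.** The strongest reply is that the outcome bearing this name is already sound. Objectives and secondary outcomes define it by SpO2, and the label sub-clinical hypoxia elsewhere confirms that meaning. The third secondary outcome covers other adverse events, which on a natural reading leaves out the item already listed. This stands: a reader might infer that the subclinical contrast itself is meaningless, but that would require footnote a to override the outcome section, and nothing says it does. The problem lies in the form and in the test of any adverse event coded from it.

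A reader might also infer that apnoea is defined by capnography and cannot occur in the control arm. The documents do not support that. Table 2 leaves apnoea undefined, and the text after Table 3 lets signs of apnoea prompt action in both groups. Ascertainment is unequal, not impossible.

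A third tempting reading is that interventions prompted by CO2 signs, which feed the Step 5 grade, are artefacts to be removed. They are not. The trial tests a monitoring-based intervention, so treatment prompted by the monitor is part of its effect. Removing it would also require unblinded staff to attribute each intervention to a trigger after randomisation.

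Finally, footnote-a events are minimal-risk descriptors and events are summarised by type, so a conclusion that the monitor causes harm is not inevitable. A true reduction in hypoxia would also work in the opposite direction. Both points temper the consequence. Neither makes the test of any adverse event a fair comparison.

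**Conclusion.** The point holds for the test of any adverse event and for any severity tabulation. As written, the plan compares counts that include an item recordable essentially only in the capnography arm, together with apnoea sought by unequal criteria. The bias runs against capnography. It does not reach the SpO2-based primary outcome or the SpO2-based subclinical outcome by this route.

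The direction follows from the text; the size does not. With equal true rates and 4 extra points, false significance is about 77–81% on an 8% base and 49–54% on a 20% base, for 810–900 per arm. A reader might take the result to be almost certain at 4 points, but these figures do not support that. It approaches certainty only with a larger excess, such as 6 points on 8% or 8 points on 20%.

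This is not a matter that can simply be left to a later analysis plan. The definition, the one-sided visibility and the test are all stated here, and control-arm CO2 that was never recorded cannot be recovered at analysis.

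**What to change.** 1. Change footnote a to the SpO2 definition in the secondary outcomes, so that the term has one meaning.
2. In the between-arm comparisons of any adverse event and of severity, count only events ascertainable by the same criterion in both arms. For apnoea, state one recording criterion that does not depend on visible CO2.
3. Report capnography-only events descriptively for the open arm, outside the test.
4. Keep interventions given in the comparison, whatever prompted them.
5. Reconcile Intervention description {11a} with {16b} and {17a} on whether the control sampling line is connected. If it is, masked control traces could be recorded and read by the same rule in both arms, and CO2-based events could then be compared.

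Items 1 to 4 cost wording on the case report form and in the analysis text. For patients already enrolled, the item would be re-derived from the SpO2 data collected for the secondary outcome. The downside is that capnography-only events become descriptive unless masked traces exist. The rate of any adverse event will also now include every patient in the SpO2 band, in both arms alike.
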